### Ethics and registration

The study protocol was approved by the ethics committee of the Hospital AGEL Trinec-Podlesi in 2022 (reference: EK 314/22) and is conducted in accordance with the Declaration of Helsinki and applicable national regulations. Written informed consent is obtained from all participants prior to any study-specific procedures. The protocol is prospectively registered at ClinicalTrials.gov [NCT07433309]. Any amendments to the protocol are reported to the ethics committee and updated in the registry before implementation.

### Eligibility criteria

Eligibility criteria are outlined in Table 1. Briefly, inclusion requires participants to be aged ≥18 years, with confirmed PAD defined by at least one of the following: resting ABI ≤0.90, duplex ultrasonography demonstrating ≥50% stenosis in a relevant lower limb vessel, or CTA demonstrating hemodynamically significant stenosis (≥50% diameter reduction) in a named below-aortic vessel associated with the presenting claudication territory, classified according to the Trans-Atlantic Inter-Society Consensus II (TASC II) anatomical severity framework and recorded at baseline. Magnetic resonance angiography (MRA) may serve as additional confirmatory diagnostic evidence for PAD diagnosis but does not substitute for CTA eligibility; patients with MRA-only imaging lacking an eligible diagnostic CTA are excluded. Participants must have Fontaine stage IIa or IIb intermittent claudication, be scheduled to participate in the institutional SET program, and have a CTA with an axial slice at the L3 vertebral level suitable for body composition analysis, acquired within 12 months prior to enrollment (the most recent eligible scan is used when multiple CTAs are available). Capacity to provide written informed consent is required. Requiring an existing diagnostic CTA selects patients who have undergone revascularization workup; the implications for external validity of this referral selection are discussed in the Limitations section. Exclusion criteria include Fontaine stage III or IV PAD; ipsilateral revascularization within six months preceding enrollment; absolute contraindication to structured exercise; cognitive impairment (Mini-Mental State Examination score <24); active malignancy expected to alter body composition independently of the exercise intervention; and estimated life expectancy <12 months, defined as the enrolling physician’s clinical judgment regarding survival likelihood based on terminal malignancy, end-stage organ failure, or documented palliative care status at screening.

### SET

The SET program follows the 2019 American Heart Association (AHA) scientific statement on optimal exercise programs for patients with PAD [19]. Each participant completes 36 supervised sessions delivered three times per week over 12 weeks, with each session lasting 60 minutes (45 minutes of structured exercise plus 15 minutes of structured patient education on vascular risk factor management and walking behavior). Treadmill exercise is initiated at 3.2 km/h on a flat gradient; participants walk until claudication pain reaches severity level 3 on a standardized four-point scale, then rest until pain subsides to level 1, repeating for five to six cycles per session.

Structured progression applies as follows: during weeks 1–4, treadmill speed increases by 0.3 km/h every two weeks to a maximum of 4.0 km/h; during weeks 5–8, treadmill grade increases by 1% every two weeks to a maximum of 3%. From week 5, resistance exercises targeting the major lower extremity muscle groups are added, beginning at two sets of 10 repetitions and progressing toward five sets at approximately 70% of one-repetition maximum. Session attendance is documented individually for each participant. Adequate adherence is defined as completion of ≥30 of 36 sessions (≥83%); non-adhering participants are retained in the primary analysis under intention-to-treat principles and analyzed separately in a pre-specified sensitivity analysis. Weekly telephone contact is maintained by a trained exercise physiologist to monitor symptoms and reinforce adherence. Participation in any other formal structured exercise program or rehabilitation intervention during the 12-week SET period is not permitted; habitual daily physical activity and unsupervised walking are allowed.

### CT body composition analysis

Body composition analysis is derived from a single axial CT slice at the L3 vertebral level. The L3 landmark is defined as the mid-vertebral body of L3, as identified on the scout image, in accordance with the methodology established by Paris et al. (2020) [20]. The L3 landmark serves as a validated systemic whole-body phenotyping tool, though it does not directly measure ischaemia-specific lower limb myopathology. This landmark demonstrates strong correlations with DXA-derived lean and fat mass (r = 0.86–0.94) [13]. Segmentation is conducted using AutoMATiCA [20], a U-Net convolutional neural network validated in multi-morbid clinical cohorts, including critically ill patients, cancer patients, those with liver cirrhosis, and organ donors. However, its performance in PAD-specific imaging, particularly in cases with prevalent vascular calcification, has not been independently verified, a limitation that will be addressed. AutoMATiCA achieves Dice similarity coefficients exceeding 0.97 for skeletal muscle, VAT, and subcutaneous adipose tissue (SAT), while achieving 0.90 for intramuscular adipose tissue (IMAT). The lower accuracy of IMAT segmentation is acknowledged, thus designating it as an exploratory rather than a primary variable in this protocol. The processing time for segmentation is approximately 350 milliseconds per scan.

Routine CTA at our center employs helical (spiral) acquisition. The L3 body composition slice is a reformatted axial image derived from the existing helical dataset, thereby incurring no additional radiation exposure.

Compartment boundaries are determined using a combination of HU thresholds and spatial-mask criteria. Skeletal muscle area is segmented within the muscle fascia boundary using an HU threshold of --29 to +150 HU; structures exceeding 150 HU, such as calcified plaque, are excluded. VAT area is segmented within the peritoneal cavity using an HU range of --150 to --50 HU. SAT area is delineated exterior to the body wall with an HU range of --190 to --30 HU. IMAT area is segmented within the muscle fascia mask, external to individual muscle boundaries, using the same HU range of --190 to --30 HU; SAT and IMAT are differentiated solely by their respective spatial masks. Skeletal muscle density is recorded as the mean attenuation value in HU across the segmented muscle compartment. Detailed parameters, thresholds, and analytical roles are presented in Table 2.

**Table 2 TB2:** Definitions, thresholds, and analytical roles of CT body composition parameters

**Parameter**	**HU range**	**Spatial mask**	**Units**	**Threshold**	**Analytical role**
Skeletal muscle density	--29 to +150	Within muscle fascia	HU (mean)	Cohort-derived; exploratory only (Youden-index derivation; see Section 2.6); not used in primary model	Primary predictor (H1; continuous z-score in primary model); predictor for secondary sarcopenic obesity classification (H3; secondary/descriptive hypothesis)
VAT area	--150 to --50	Within peritoneal cavity	cm^2^	Cohort-derived, sex-specific; exploratory only (see Section 2.6); not used in primary model	Primary predictor (H2; continuous z-score in primary model); predictor for secondary sarcopenic obesity classification (H3; secondary/descriptive hypothesis)
SMI	--29 to +150	Within muscle fascia	cm^2^/m^2^		Covariate in pre-specified secondary expanded model only (not included in primary model); exploratory predictor of sarcopenia by mass
SAT area	--190 to --30	Exterior to body wall	cm^2^	—	Covariate in pre-specified secondary expanded model only (not included in primary model)
IMAT area	--190 to --30	Within fascia, exterior to individual muscle boundaries	cm^2^	—	Exploratory variable

Abbreviations: CT, computed tomography; HU, Hounsfield units; IMAT, intramuscular adipose tissue; SAT, subcutaneous adipose tissue; SMI, skeletal muscle index; VAT, visceral adipose tissue.

Quality control procedures include verification that calcified plaque is excluded from the muscle compartment, flagging scans with an inter-compartment boundary coefficient of variation exceeding 35% for consensus adjudication by two independent analysts, and benchmarking inter-analyst agreement on the first 20 scans of the series prior to full enrollment. This is assessed using Bland-Altman analysis and the intraclass correlation coefficient (ICC). A pre-specified ICC threshold of ≥0.90 is required for both skeletal muscle density and VAT area before proceeding to full enrollment. If the ICC falls below 0.90 on the 20-scan benchmark, the segmentation protocol will be reviewed, and analysts retrained; an additional benchmark of 10 scans will be conducted before full enrollment begins. Baseline body composition (T0) is derived from existing diagnostic CTA scans, with the most recent scan selected when multiple eligible CTAs are available within a 12-month window. A standardization and inter-scanner variability policy will be documented prior to the first enrollment and applied throughout the multi-year enrollment period; any scanner upgrades or protocol changes will also be documented and assessed for their potential impact on HU consistency.

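### The CT agreement gate retests a failed 20-scan benchmark on only 10 scans, so the retest discriminates less well than the test it follows

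*Protocol article*

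**What the plan says.** The quality-control paragraph under CT body composition analysis (Protocol article) plans "benchmarking inter-analyst agreement on the first 20 scans of the series prior to full enrollment", assessed by Bland-Altman analysis and the ICC. The pass rule is: "A pre-specified ICC threshold of ≥0.90 is required for both skeletal muscle density and VAT area before proceeding to full enrollment". The action on failure is: "If the ICC falls below 0.90 on the 20-scan benchmark, the segmentation protocol will be reviewed, and analysts retrained", after which "an additional benchmark of 10 scans will be conducted before full enrollment begins".

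The rule is a point estimate. It has no confidence limit, and no acceptance limit is attached to the Bland-Altman analysis. The 0.90 limit is not restated for the 10-scan retest, although the general requirement can be read as covering it. No reason is given for making the retest smaller. Both measures enter the primary model as z-scores standardised within the cohort (Statistical analysis, analytical hierarchy and primary model specification).

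**The concern.** A reading process reaches the retest only after it has failed, so the retest should be at least as discriminating as the first test. With half the scans it has more sampling error. Agreement below 0.90 is then more likely to be passed by chance, and agreement that retraining has genuinely made good is more likely to be rejected.

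Agreement below the intended standard adds measurement error to skeletal muscle density or VAT area, which attenuates the H1 and H2 estimates and costs some power. A second issue follows from the same step. If the review changes the segmentation protocol and the benchmark scans are cohort scans, they need to be re-read. Otherwise two reading protocols would be mixed in one z-score.

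**Working it through.** The plan gives no pass probability or precision for the gate, so there is no stated figure to reproduce.

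**Inputs from the protocol.** First benchmark n = 20, retest n = 10, limit 0.90, both measures required. For the power step: 100 evaluable participants, 40 failures, about 80% power at α = 0.05 (Sample size), and p < 0.025 per hypothesis (Statistical analysis).

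**Assumptions.** Two analysts (k = 2); the number is not given for the benchmark, but flagged scans go to "consensus adjudication by two independent analysts". Normal errors, no systematic analyst bias, and the 0.90 limit applied to the retest.

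**Pass probability for one measure.** With k = 2 and the consistency form of the ICC, MSB/MSE is distributed as [(1+ρ)/(1−ρ)] × F(n−1, n−1). An observed ICC of 0.90 corresponds to MSB/MSE = 1.90/0.10 = 19, so

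P(pass) = P( F(n−1, n−1) ≥ 19 / [(1+ρ)/(1−ρ)] ).

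| True ICC | (1+ρ)/(1−ρ) | F needed | n = 20 | n = 10 |
|---|---|---|---|---|
| 0.80 | 9.00 | 2.111 | 5.6% | 14.0% |
| 0.85 | 12.33 | 1.541 | 17.7% | 26.5% |
| 0.95 | 39.00 | 0.487 | 93.7% | 85.0% |

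The one-way form of the ICC and a simulation of the absolute-agreement ICC(2,1) agree within about 1 to 2 points. The 95% CI around an observed ICC of 0.90 is about 0.77 to 0.96 with 20 scans and 0.65 to 0.97 with 10.

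**Two rounds, if retraining changes nothing (an upper bound).** P = p₂₀ + (1 − p₂₀) × p(retest).

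- One measure, true 0.85, 10-scan retest: 0.177 + 0.823 × 0.265 = 0.395.
- One measure, true 0.85, 20-scan retest: 0.177 + 0.823 × 0.177 = 0.323.
- One measure, true 0.80: 0.056 + 0.944 × 0.140 = 0.189 with 10 scans; 0.056 + 0.944 × 0.056 = 0.109 with 20.

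**Both measures required, both at the same true ICC, independent errors.** Square the per-round probabilities.

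- True 0.85: p₂₀² = 0.031 and p₁₀² = 0.070. Two rounds: 0.031 + 0.969 × 0.070 = 0.099 with a 10-scan retest, and 0.031 + 0.969 × 0.031 = 0.062 with a 20-scan retest.
- True 0.80, 10-scan retest: 0.003 + 0.997 × 0.020 = 0.023.

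With positively correlated errors, or only one deficient measure, these move towards the one-measure figures.

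**Consequence for power.** Taking the stated 80% power at two-sided 0.05 as given, the noncentrality is 1.96 + 0.84 = 2.80. This corresponds to a log odds ratio per SD of 2.80/√(100 × 0.4 × 0.6) = 2.80/√24 = 0.572. Reliability R multiplies the noncentrality by √R, and the critical value at p < 0.025 is 2.241.

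- R = 0.90: Φ(2.656 − 2.241) = Φ(0.415) = 66%.
- R = 0.85: Φ(2.581 − 2.241) = Φ(0.340) = 63%.

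The difference is about 3 points, before covariate adjustment.

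**A larger benchmark.** With n = 50, the same formula gives a pass probability of 6.7% at true 0.85, 0.5% at 0.80 and 99.3% at 0.95.

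**The case against.** A reader might infer that inadequate reading often gets through. The documents do not support that. Both measures must reach 0.90, so two clearly deficient measures rarely pass (about 2% at 0.80 and 10% at 0.85 over two rounds, with independent errors). The higher figures apply when a single measure lies modestly below the limit. All two-round figures also assume that the required review and retraining achieve nothing.

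A reader might also take this gate to be the only quantitative safeguard for the two predictors. It is not. The same paragraph flags scans with a boundary coefficient of variation above 35% for adjudication, and the CT acquisition protocol section plans 10 phantom or repeated-scan controls a year with HU drift reported. Segmentation is automated, which should limit analyst variation. The gate is, however, the only pass/fail criterion for agreement between analysts, and the protocol itself says that the algorithm's performance in PAD imaging has not been independently verified.

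Measuring the power loss against error-free reading would overstate the harm, because the gate promises 0.90, not 1.00. It would also be too strong to say that a second failure has no consequence: the 0.90 requirement before full enrolment, read plainly, would remain unmet. Whether the benchmark comes too late depends on what is meant by the series and on how full enrolment is read, so no timing criticism can be built on it.

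Finally, equalising the retest at 20 scans gains only a moderate amount (40% to 32% for one measure at 0.85), and re-reading of early scans may be covered in an imaging manual that is not shown. Both points are fair and limit the size of the finding. Neither gives a reason for a smaller retest.

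**Conclusion.** The point holds as a modest, inexpensive improvement to a stated rule. A 10-scan retest after a failed 20-scan benchmark is worse in both directions: it is more lenient to agreement of 0.80 to 0.85 and harsher to agreement of 0.95. For one measure at true 0.85, the two-round pass probability is at most about 40%, against 32% with an equal-sized retest; for two such measures with independent errors it is about 10% against 6%. The cost of letting reliability of 0.85 through instead of 0.90 is about 3 points of H1 power (66% to 63%).

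These figures rest on two analysts, normal errors, no systematic analyst bias, the 0.90 limit applied to the retest, and inter-analyst ICC standing in for the whole reliability of the predictor.

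**What to change.** In the quality-control paragraph:

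1. Make the retest at least 20 scans, different from those in the failed benchmark. Archived PAD CTAs from the centre may be used. A larger set, such as 50, would cut first-round passing for one measure at true 0.85 to about 7%.
2. State that the same rule, ICC at least 0.90 for both measures, applies to the retest.
3. Report the ICC with its 95% CI at each benchmark.
4. If the segmentation protocol is revised, re-segment all earlier cohort scans under the final version before z-scores are formed.

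The cost is analyst time for some tens of single slices (automated segmentation takes about 350 milliseconds per scan) and a few sentences of protocol text. No additional patients or CT acquisitions are needed.

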#### CT acquisition protocol

CTA at our center is performed on a Siemens SOMATOM Force (Siemens Healthineers, Erlangen, Germany) utilizing helical acquisition with standard parameters: tube voltage of 100–120 kVp; tube current of 200–350 mAs (with automated exposure control); and slice thickness of ≤3 mm (reconstruction interval of 1.0–1.5 mm). Contrast-enhanced studies utilize iodinated low-osmolality contrast media (iohexol or equivalent), with a weight-based dose calculation of 1.5 mL/kg, capped at 150 mL. Bolus tracking is employed for timing the arterial phase (trigger threshold of 100 HU in the descending aorta, with a scan delay of 6–8 seconds post-trigger). Body composition HU measurements are conducted on post-contrast arterial-phase images, consistent with methods used in prior validation studies for this cohort [16]. Artificial intelligence (AI)-based noise reduction is not currently implemented in the clinical reconstruction pipeline. Images are reconstructed using a soft-tissue kernel (Siemens Br40 or equivalent), a parameter that remains constant across all study acquisitions and directly influences absolute HU values in body composition analysis. Iterative reconstruction techniques, specifically Sinogram Affirmed Iterative Reconstruction (SAFIRE) at strength 3, are employed, or an equivalent method is utilized based on the institutional protocols at the time of image acquisition. The imaging matrix is configured to 512 × 512, with a field of view ranging from 350 to 450 mm, tailored to the patient’s habitus, yielding a pixel size of approximately 0.68 to 0.88 mm. Both parameters are documented in the study log, and any deviations from standard settings are recorded and assessed for their impact on HU calibration. Post-acquisition processing for body composition analysis employs the AutoMATiCA neural network [20] applied to the single reformatted axial slice at the L3 mid-vertebral body level. No additional post-processing beyond segmentation and HU measurement is performed. All scans are acquired and reconstructed using a single standardized institutional protocol; any deviations are documented in the study log and evaluated for their potential impact on HU calibration. Inter-scan variability arising from the multi-year enrollment period will be monitored by including 10 phantom or repeated-scan quality controls annually, with HU drift quantified and reported.

### Body composition parameters and sarcopenic obesity classification

Body composition parameters, HU thresholds, spatial masks, derivation, units, and analytical roles are specified in Table 2. In the primary model (H1 and H2), skeletal muscle density and VAT area are entered as continuous standardized z-scores (mean 0, SD 1), facilitating direct comparison of effect estimates on a common scale. Nonlinearity of each continuous predictor is assessed using restricted cubic splines (three to five knots, selected based on the Akaike Information Criterion). The primary predictor for H1 is skeletal muscle density (HU). The exploratory classification threshold for low skeletal muscle density (myosteatosis) will be derived from this cohort by maximizing the Youden index (sensitivity + specificity -- 1) against the binary primary composite outcome, implemented using the cutpointr R package with 1000-sample bootstrap confidence intervals (CIs). This threshold derivation is explicitly designated as exploratory and hypothesis-generating; it is not included in the primary predictive analysis, which utilizes the continuous z-score. Derived thresholds are subject to substantial optimism in a derivation cohort and require external validation before clinical application. This approach is preferred over adopting thresholds from the oncological literature—specifically, the body mass index (BMI)-stratified values reported by Martin et al. [21] (41 HU for BMI < 25 kg/m^2^; 33 HU for BMI ≥ 25 kg/m^2^) or the Health, Aging, and Body Composition (ABC) Study mid-thigh attenuation reference [22]—as neither has been validated in a PAD population, and the biological relationship between muscle lipid infiltration and aerobic exercise adaptation in chronic limb ischaemia may differ significantly from oncological or elderly community contexts. Sensitivity analyses applying the thresholds from Martin et al. (33 HU and 41 HU; see Table 3, sensitivity analyses #8 and #9) are pre-specified to facilitate direct comparison with the cohort-derived threshold.

**Table 3 TB3:** Pre-specified sensitivity and secondary analyses

**#**	**Analysis**	**Rationale**
1	Alternative composite threshold: ≥40% relative MWD gain	Tests sensitivity of the primary outcome to a more conservative functional threshold
2	Alternative composite threshold: ≥60% relative MWD gain	Tests sensitivity to a more stringent functional threshold
3	Alternative composite threshold: ≥100 m absolute MWD gain	Tests sensitivity to an absolute rather than relative distance criterion
4	Functional improvement component only (no revascularization criterion)	Isolates the predictive relationship with functional adaptation. Mandatory pre-specified secondary analysis; reported in all primary publications regardless of composite outcome result.
5	Revascularisation-free survival component only	Isolates the predictive relationship with intervention requirement. Mandatory pre-specified secondary analysis; reported in all primary publications regardless of composite outcome result.
6	Restriction to guideline-concordant revascularisation events only	Removes patient-preference-driven events to reduce confounding; specifically examines discordant cases (functional improvement achieved but revascularisation occurred)
7a	Four-predictor model: muscle density, VAT, age, sex (excluding baseline MWD)	Robustness check with an EPV approximately 10; tests stability of primary model estimates when baseline MWD is excluded
7b	Three-predictor model (muscle density, VAT, age; excluding sex)	Robustness check with an EPV approximately 13–14
8	Alternative muscle density threshold: 33 HU	Tests lower threshold sensitivity for myosteatosis classification (Martin et al. [21] value for BMI ≥ 25 kg/m^2^); see also Section 2.6
9	Alternative muscle density threshold: 41 HU [Martin et al. [21], BMI < 25 kg/m^2^ stratum]	Tests higher threshold sensitivity for myosteatosis classification; see Section 2.6
10	Alternative VAT threshold: --20 cm^2^ (110 cm^2^ M; 80 cm^2^ F)**†**	Tests sensitivity to a more conservative VAT threshold
11	Alternative VAT threshold: +20 cm^2^ (150 cm^2^ M; 120 cm^2^ F)**†**	Tests sensitivity to a more stringent VAT threshold
12	Adherent subgroup (≥30/36 sessions completed)	Per-protocol analysis to assess treatment-specific effects
13	30% treatment failure rate scenario (approximately 30 failures)	Reports model performance and power under a more optimistic clinical assumption
14	Expanded confounding model: primary five predictors plus ABI, smoking status, diabetes, Clinical Frailty Scale score, TASC II classification, SMI, SAT	Pre-specified secondary expanded model; EPV approximately 3–4 (acknowledged limitation); designated as robustness sensitivity analysis; tests whether primary predictor associations are independent of additional clinical confounders
15	Complete-case sensitivity analysis	Comparison with the primary MICE-based analysis to assess the impact of the missing-at-random assumption; all cases with complete data on the five primary predictors and primary outcome are included

† Reference VAT thresholds utilized for sensitivity offsets are 130 cm^2^ for men [23] and 100 cm^2^ for women [24]. Sensitivity bounds are tested with ±20 cm^2^ offsets around these reference values. Abbreviations: ABI, ankle–brachial index; BMI, body mass index; EPV, events per variable; F, female; HU, Hounsfield units; M, male; MICE, multiple imputation by chained equations; MWD, maximum walking distance; SAT, subcutaneous adipose tissue; SMI, skeletal muscle index; TASC II, TransAtlantic Inter-Society Consensus II; VAT, visceral adipose tissue.

The primary predictor for H2 is VAT area (cm^2^). Exploratory sex-specific classification thresholds for elevated VAT will be derived separately for men and women by maximizing the Youden index against the binary primary composite outcome, using the same cutpointr bootstrap framework. This threshold derivation is explicitly designated as exploratory and hypothesis-generating, with the continuous z-score employed in the primary model. This approach is preferred over adopting general-population thresholds (>130 cm^2^ in men and >100 cm^2^ in women) from weight-loss and metabolic studies in non-PAD populations [23, 24], as the VAT level at which pro-inflammatory signaling meaningfully constrains exercise adaptation in claudicants has not been established. Sensitivity analyses applying the literature-derived VAT thresholds [23, 24] are pre-specified in Table 3 (sensitivity analyses #10 and #11). The biological rationale for VAT as a cardiometabolic risk marker is discussed in the Introduction [14]. The skeletal muscle index (SMI; cm^2^/m^2^) and SAT area are designated as covariates in the pre-specified secondary expanded model only; they are excluded from the primary model (see Section 2.12). IMAT area is analyzed as an exploratory variable. H3—sarcopenic obesity—is operationally defined as a secondary/descriptive hypothesis by the co-occurrence of skeletal muscle density below the cohort-derived exploratory threshold and VAT area above the cohort-derived sex-specific exploratory threshold, resulting in a four-group phenotype classification: normal (reference group), isolated low muscle density, isolated elevated VAT, and sarcopenic obesity. H3 is not included in the family-wise Bonferroni correction.

